**Fig 1 pone.0303837.g001:**
[figure not shown]
UBI model of impact (adapted from Johnson et al, 2021 [51]).

The highly politicised nature of basic income experiments underlines the importance of clear and comprehensive evaluation. The scheme in Ontario, that was abruptly cancelled after a change in government, illustrates the potentially negative effects of political intervention. This resulted in no evaluation findings due to a lack of data and the fact researchers are bound by confidentiality agreements [54]. Even in cases where evaluations have reported as planned, an absence of comprehensive evaluation or clarity around anticipated outcomes has sometimes left pilots and trials of basic incomes vulnerable to ‘spin’ [21,55]. This is partly related to how findings have been framed in the published literature. As noted above, the Finnish trial found no negative impact on labour market participation. However, evaluators failed to make clear that the expectation of critics of basic income was that it would cause a *reduction* in labour market participation through ‘free-riding’, and hence that no change represented a finding in favour of BI. For example, Verho et al [46] concluded “The Finnish experiment failed to produce any sizeable short-term employment effects despite offering larger improvements in employment incentives than any realistic nationwide policy could provide” (p. 27), without acknowledging this context.

A more fundamental weakness of that trial is that it failed to measure health impacts comprehensively using validated measures in ways that would have advanced evidence on the pathways and nature of causality. Similarly, the Finnish trial presented positive findings in relation to subjective wellbeing, but without baseline data, which meant these could not be attributed to BI [25]. The absence of robust and validated outcome measures that could also be used by health economists deprived the trial of key evidence on overall costs and benefits, with recent work by Johnson, Johnson, Pickett and colleagues highlighting the importance of employing comparable measures that can be used in microsimulation to model longer-term impacts at population level [44]. A weakness of the evidence base more generally is that long-term impacts have not been adequately evaluated due to the relatively short duration of most pilots [56].

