### Impact evaluation

To measure impact the design incorporates a suite of quasi-experimental designs (QEDs) which will enable triangulation between multiple data sources and provide a robust account of the difference the BIP makes to care leavers in Wales. QEDs attempt, in the absence of randomisation, to achieve identification of the causal impact of one or more interventions, primarily through a mix of sample selection and statistical approaches [63]. Randomisation is not possible in this case because the BIP is open to all eligible young people and starts at the same point for all participants (the month after their 18^th^ birthday). The QED approach will enable us to determine that, conditional on our sample selection and analytical strategy, we do not expect to see any uncontrolled-for differences between the intervention and counterfactual groups, and so any differences between the two groups can be attributed to the BIP. Further detail about our analysis plan is available in supplementary materials.

We aim to compare the outcomes of care leavers who turn 18 during the enrolment year (and are thereby eligible for the BIP), to outcomes of care leavers in Wales who turn 18 the following year. This will involve two quasi-experimental approaches: coarsened exact Matching (CEM) and difference in differences (DID). Measurement will take place at two time points. Baseline data will be gathered around the individual’s 18^th^ birthday (referred to below as time t-1) and follow-up data will be gathered around their 20^th^ birthday (referred to below as time t).

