#### Outcomes and data sources

The Welsh Government identified six outcome domains of interest, and the literature suggests that it is also important to include physical and mental health outcomes more broadly. These, and the means of collection through surveys and administrative records, described below, are outlined in Table 1.

**Table 1 pone.0303837.t001:** Outcomes and data sources.

Outcome domain	Collected through	Specific measures
Wellbeing/ psychological Wellbeing	Survey Data	Categorical indicators of frequency of emotional states, level of anxiety, happiness, feelings of positivity, including an open-ended question
Financial literacy/ security	Survey Data	Questions on levels of financial coping, allocation of income, spending habits with an open-ended question on money management.
Community cohesion/ engagement	Survey Data	Binary indicators of friendship, partnership, owning a pet, having a person of trust, and categorical indicators of emotional support. Binary indicators of community cohesion in follow up (t) survey
Ameliorating the effects of poverty	Survey and administrative data	Categorical indicator of current housing, binary indicator of housing satisfaction Leisure and access to luxury items/internet
Access to labour market/ education/ lifelong learning	Administrative data	Binary indicator of employment; continuous measure of earnings; binary indicator of enrollment in education or training; binary indicator of participation in higher education; binary indicator of participation in further education. These outcomes will be extended using linked longer-term data from the Longitudinal Education Outcomes (LEO) data.
Volunteering and life skills	Survey Data	Education, employment and training.
Physical and mental health	Survey and administrative data	Self-rated general health (ONS question) Limiting long-term illness (ONS question) Common mental disorders: depression (PHQ-2); anxiety (GAD-2).

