*Difference in differences*. Difference in Differences approaches are quasi-experimental approaches which compare the differences between treated and counterfactual units, before and after the introduction of a new policy or intervention (Fig 1 below). This comparison allows for time invariant differences, whether observed or unobserved to be controlled for analytically [66]. We will undertake two different versions of the difference in difference approach for our two separate data sources. For administrative data, we will make use of a standard difference in difference in which participants in Wales are compared with matched English care leavers, covering the same time period (and same life stage) as the Welsh Data. For our survey outcomes, due to the challenges associated with collecting data from English care leavers, we will instead draw our counterfactual group from the subsequent cohort of Welsh care leavers. Although the comparison of two groups that have not been measured contemporaneously (as is the case comparing Welsh Care leavers in one cohort with Welsh Care leavers in another) is a non-standard implementation of the difference in differences methodology, the underlying assumptions remain the same. Instead of assuming common trends in the macroeconomic conditions (as would be the case for a standard DID), we are instead assuming common trends over the same period of the life course – that is, we assume that outcomes change in the same ways for young people between their 18^th^ and 20^th^ birthday, for young people whose 18^th^ birthdays were up to a year apart. The broad approach to a Difference in Differences approach can be seen in Fig 2.

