#### Statistical methods for analysis of impact

Our analytical strategy for the survey data will follow a matched difference in differences approach. Matching will take place prior to analysis in order to select the most appropriate sample.

The difference in difference strategy for this data will be to take the first time period as baseline survey data for both the treatment and counterfactual groups, and to make use of the endline survey data as the second time period.

*Imputation strategy*. Inspection of the missing data pattern will provide some initial insight in the type of missingness, and statistical testing will further help assess whether the missing data mechanism is Missing Completely At Random (MCAR) or Missing At Random (MAR). We will utilise Little’s MCAR test [68], which determines whether the missingness is related to the observed and unobserved data. We will also use a logistic regression model with an indicator of missingness as the outcome, which will show whether relevant covariates are predictive of missingness, pointing towards the plausibility of a MAR assumption.

Due to the nature of survey data collection, we anticipate missing data for some participants. We will not make use of imputation for outcome measures as this carries substantial risks in terms of bias. For missing data at baseline we will make use of a mixture of Multiple Imputation through Chained Equations (MICE) [69], in which available baseline or demographic data for the participant are used in regression analyses to calculate the likely values of the missing variable. Following imputation of missing data, we will examine the convergence diagnostics to ensure that the imputation process is stable and the imputed values are plausible.

*Analytical specification*. *Primary analysis – surveys*. Our primary analysis specification will be conducted using ordinary least squares/linear prediction model regressions, specified as;

$$Y_{ilt}=\alpha +\;\beta_{1}Y_{ilt-1}+\beta_{2\;}B_{l}+\Gamma_{1}X_{i}+\Gamma_{2}L_{l}+\epsilon_{lt}$$

Where;

*Y*_*ilt*_ is the outcome measure for individual i in local authority l at endline.

*α* is a regression constant

*Y*_*ilt*−1_ is the lagged value of the participant’s outcome measure at baseline.

*B*_*l*_ is a binary indicator of whether the participant was eligible for the basic income payments, set to 1 if they are and 0 else (equivalent to a binary indicator for being in the eligible cohort

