*X*_*i*_ is a vector of participant level characteristics.

*L*_*l*_ is a vector of local authority fixed effects

*ϵ*_*lt*_ is an error term clustered at the level of the local authority/time period level.

*Follow-up (t) only data*. Some variables in the survey are only collected at follow-up (time t), and not at baseline (time t-1). For these variables, we will adopt a less typical approach and replace *Y*_*ilt*−1_ with a vector of baseline variables that are the strongest control group predictors of the outcome at time t.

*Primary analysis - administrative data*. Our primary analysis specification will be conducted using ordinary least squares/linear prediction model regressions, specified as;

$$Y_{ilt}=\alpha +\;\beta_{1}T_{t}+\beta_{2\;}B_{l}+\beta_{3}(T_{t}\cdot B_{l})+\Gamma_{1}X_{i}+\Gamma_{2}Q_{l}+\epsilon_{lt}$$

Where;

*Y*_*ilt*_ is the outcome measure for individual i in local authority l in time t.

*α* is a regression constant

*T*_*t*_ is a binary indicator of whether or not the time period in question is that in which the intervention is active.

*B*_*l*_ is a binary indicator of whether the participant was in a local authority that would make them eligible for the basic income payments, set to 1 if they are and 0 else (equivalent to a binary indicator for being in Wales).

(*T*_*t*_∙*B*_*l*_) is an interaction term between treatment local authority and treatment time period, which takes values of 1 only for Welsh local authorities during the time period when the intervention is active. This is our treatment variable and its coefficient is our coefficient of interest.

X_i_ is a vector of participant level characteristics.

*Q*_*l*_ is a vector of local authority level characteristics including those used in matching.

*ϵ*_*lt*_ is an error term clustered at the level of the local authority/time period (the level at which the treatment status varies).

*Secondary Analysis*. Secondary analysis will follow the same regression specification as our primary analysis, but replacing the variable Y with the relevant secondary outcomes.

*Robustness Checks*. We will robustness check our analyses by:

Using Null imputation across the board, replacing MICEConducting complete case analysisUsing logistic and probit regression for binary outcomes

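### Survey items collected only at follow-up are analysed as an adjusted endline comparison of two cohorts, not as a difference in differences, and the attribution claim makes no exception for them

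*Protocol article*

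**What the plan says.** Under Statistical methods for analysis of impact, the survey strategy is declared in one sentence: "Our analytical strategy for the survey data will follow a matched difference in differences approach". The baseline survey is the first period and the endline survey the second. The equation given for the primary survey analysis regresses the endline outcome on its own baseline value, an indicator of the eligible cohort, participant characteristics and local authority fixed effects.

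The paragraph on follow-up (t) only data then says: "Some variables in the survey are only collected at follow-up (time t), and not at baseline (time t-1"). For these it calls the approach less typical and replaces the lagged outcome "with a vector of baseline variables that are the strongest control group predictors of the outcome at time t". Nothing else in the model changes, so the cohort coefficient is still the effect estimate.

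Table 1 identifies one such set, in the community cohesion/engagement row: "Binary indicators of community cohesion in follow up (t) survey". The other items in that row (friendship, partnership, pet, person of trust, emotional support) are not marked as follow-up only. The text after Table 1 promises published effects on all its outcomes.

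Three other places bear on this:

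- The Difference in differences paragraph gives the reason for the design: "This comparison allows for time invariant differences, whether observed or unobserved to be controlled for analytically". For the survey it adds: "we will instead draw our counterfactual group from the subsequent cohort of Welsh care leavers".
- The Impact evaluation section says that, conditional on sample selection and analytical strategy, "any differences between the two groups can be attributed to the BIP".
- The section Research on basic income says that the Finnish trial reported positive wellbeing findings "but without baseline data, which meant these could not be attributed to BI". The overview of basic income schemes says participants in that trial were selected at random.

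**The concern.** A difference in differences needs two measurements of the same outcome. An item first asked at follow-up has neither a change nor a lagged value. What remains is a comparison of endline levels between the 2022-23 and 2023-24 cohorts, adjusted for other variables. The removal of unobserved time-invariant differences, which is the stated reason for the design, is lost for these items. Choosing covariates because they predict the outcome among controls does not ensure that they carry whatever distinguishes the two cohorts.

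The article does not say this. Calling the approach less typical discloses a change of covariate, not a change in what the coefficient identifies. The attribution sentence has no exception for these items. None of the listed robustness checks (null imputation, complete cases, logistic or probit models) addresses a missing baseline outcome. The article also withholds attribution from a randomised trial because it lacked baseline data.

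What is at stake is how the cohesion indicators are read. More cohesive communities is one of the policy goals that the article cites, and these indicators could be presented as BIP effects on the same footing as outcomes that have a baseline.

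**Working it through.** **Inputs from the article.** Recipients: 635. Final baseline response in the intervention group: 64%. Anticipated detectable survey effect: 0.2 SD. The article gives no alpha, power or formula for that last figure, so it cannot be strictly reproduced. With two-sided 5%, 80% power and 0.64 × 635 = 406 per group, (1.96 + 0.84) × √(2/406) = 0.197 SD, which is consistent with it before follow-up loss, matching loss or clustering. It serves here only as a yardstick.

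**Assumptions (not in the article).** Follow-up retention is 70% in equal cohorts, so 406 × 0.70 ≈ 284 each. The outcome is a stable part U plus noise, with total variance 1 and var(U) = 0.5 (stability 0.5). A stable cohort gap d in U exists before any payment, and the true effect is zero. There is no matching, participant covariate or local authority adjustment. The proxies carry U, and so part of the gap, and explain a share R² of the endline outcome.

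**Formula.** Write the proxy index as U plus noise of variance v. Its slope on the outcome is 0.5/(0.5 + v), and R² = 0.25/(0.5 + v), so the slope equals R²/0.5. The index itself shifts by d between cohorts. The bias left in the cohort coefficient is therefore

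bias = d × (1 − R²/0.5).

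The real lagged outcome is the special case v = 0.5, which gives R² = 0.25. The approximate standard error is √(2(1 − R²)/284).

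**Results for d = 0.2 SD**

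| Model | Bias (SD) | SE | False positives, two-sided 5% |
|---|---|---|---|
| Proxies, R² = 5% | 0.2 × 0.9 = 0.18 | 0.082 | about 60% |
| Proxies, R² = 10% | 0.2 × 0.8 = 0.16 | 0.080 | about 52% |
| Proxies, R² = 20% | 0.2 × 0.6 = 0.12 | 0.075 | about 36% |
| Lagged outcome, as planned where a baseline exists | 0.2 × 0.5 = 0.10 | 0.073 | about 28% |
| Change-score difference in differences | 0.00 | – | about 5% |

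Simulation of the same set-up agrees (58%, 52% and 36% for the three proxy rows).

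**Excess due to the missing baseline.** The right comparator is the model the article plans for other survey outcomes, which is the lagged-outcome regression and not a change score. The excess is 0.18 − 0.10 = 0.08, 0.16 − 0.10 = 0.06 and 0.12 − 0.10 = 0.02 SD. For d = 0.1 SD every bias halves, and the excess is 0.04, 0.03 or 0.01 SD.

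**Sensitivity to the assumed process.** A second simulation used d = 0.2 SD, outcome autocorrelation 0.6, and a proxy correlated 0.3, 0.5 or 0.7 with the unmeasured baseline.

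- Stable gap: the proxy model leaves 0.19, 0.17 or 0.14 SD, and 0.20 SD if the proxy does not carry the gap. The real lagged outcome leaves 0.08 SD.
- Gap that decays with the outcome: the proxy model leaves 0.11, 0.09 or 0.065 SD, and 0.12 SD if the proxy does not carry the gap. The real lagged outcome leaves 0.00. A change score would over-correct here, by 0.6 × 0.2 − 0.2 = −0.08 SD.

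The excess under this second model is thus about 0.06 to 0.12 SD. Its size depends on the assumptions; its presence does not, as long as a gap exists and the proxies capture less of it than the real baseline would. With a baseline the gap can be seen and both models run. Without one, neither is possible.

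**The case against.** Much can be said for the plan.

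- **The gap is assumed.** Nothing in the article supports 0.1 or 0.2 SD, or the R² values. The cohorts are successive years of Welsh care leavers from the same local authorities, split by birth date, with 97% take-up. This stands: size and direction are unknown.
- **Planned adjustment is left out of the illustration.** Individual matching (including on local authority where possible), participant covariates and local authority effects may absorb part of a gap. This stands, so only the uncaptured part enters the coefficient.
- **The survey model is not a change score in any case.** Outcomes with a baseline also keep some bias from a stable gap. This stands, and it reduces the cost of the missing baseline to the excess shown above.
- **The attribution sentence is conditional** on sample selection and analytical strategy, and the Discussion concedes that differing conditions between cohorts limit confidence. Both are fair, but neither is tied to the items for which the strategy loses its first period.
- **The Finnish parallel is not exact,** since other baseline variables exist here and are adjusted for. True, but the outcome's own baseline is missing, and there is no randomisation to make up for it.
- **Detail may sit in the analysis plan.** Predictor lists and table layout may well do so. The substitution itself and the unrestricted claim are stated in the article.

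A reader might go further and infer that any prior cohort difference passes intact into the reported effect, that the whole community domain is affected, or that selecting predictors among controls causes the bias. The documents do not support these readings. Other adjustment is planned, only the cohesion indicators are marked follow-up only, and with no cohort gap the proxy model holds its 5% error rate. The source of the problem is confounding, not the selection step.

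**Conclusion.** The concern holds in limited form. For follow-up-only survey items the specified model does not deliver the property that the article claims for difference in differences. Whatever part of an earlier cohort difference escapes the adjustments is counted as effect, and the data cannot reveal it. By the article's own standard for the Finnish findings, these results should not be attributed to BIP without qualification.

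On the main illustration the excess over the planned lagged-outcome model is 0.02 to 0.08 SD for an assumed stable gap of 0.2 SD; the alternative process gives 0.06 to 0.12 SD. The total bias of 0.12 to 0.18 SD approaches the 0.2 SD that the study expects to detect, but 0.10 SD of it would remain under the planned model even with a baseline. It would be wrong to set the full 0.12 to 0.18 SD against zero as the price of the missing baseline. These figures are illustrations and do not estimate bias in this study. What needs correcting is the label and the claim for a small set of outcomes, not the survey analysis as a whole.

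**What to change.** 1. In the paragraph on follow-up (t) only data, label these items as adjusted endline cohort comparisons and report them apart from the outcomes that have a baseline.
2. State there that the removal of unobserved time-invariant differences (Difference in differences) and the attribution sentence (Impact evaluation) do not extend to them, in line with the standard applied to the Finnish trial.
3. Beside each estimate, give the residual pre-existing cohort difference, in SD, that would fully explain it, and say what persistence is assumed. If the difference persists fully, this is the estimate itself in SD units; if it persists at 0.6, it is the estimate divided by 0.6.

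The choice of predictors in the control group can stay. It keeps treatment effects out of covariate selection, and a fixed list that predicted less well could leave more bias.

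The cost is a few sentences and one extra table column, and a weaker causal claim for these items. No new data are needed.

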#### Study setting

The study will be conducted in Wales across all 22 local authority areas. Local authorities are the lowest level of elected government in Wales, and are responsible for delivering Children’s Social Care Services.

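### Clustering by local authority/time period is the wrong unit for the administrative difference in differences and unsafe for the survey model; cluster both by local authority

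*Protocol article*

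**What the plan says.** All references are to the protocol article, mainly its section Statistical methods for analysis of impact.

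- **Survey model.** Each person contributes one endline outcome, regressed on the baseline value, a treatment indicator, personal characteristics and authority terms. The treatment indicator is "equivalent to a binary indicator for being in the eligible cohort". The authority term "is a vector of local authority fixed effects". The error "is an error term clustered at the level of the local authority/time period level".
- **Administrative model.** This is a period-by-Wales interaction model. Its authority term "is a vector of local authority level characteristics including those used in matching", so it has no authority fixed effects. Its error "is an error term clustered at the level of the local authority/time period (the level at which the treatment status varies").
- **Meaning of time period.** For the survey data the strategy is to "take the first time period as baseline survey data for both the treatment and counterfactual groups", with the endline survey as the second period. The Impact evaluation section adds: "Measurement will take place at two time points", around the 18th and 20th birthdays.
- **Size.** The study runs "across all 22 local authority areas".

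The listed robustness checks concern imputation, complete cases and logistic or probit models. None varies the clustering level.

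**The concern.** Observations that share an error component belong in one cluster. In the administrative model, an authority's two periods share persistent authority differences and, where the same people are followed, persistent personal differences. These largely cancel in a before/after contrast. Clusters that separate the periods cannot see the cancellation, so the variance is misstated.

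In the survey model, treatment varies within an authority only by cohort. An analyst who applies the administrative model's stated rationale to the survey data would form authority-by-cohort cells, two per authority, alongside authority fixed effects. That combination understates the variance.

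The administrative results cover employment, earnings and education, where real effects could be missed. The survey results carry wellbeing, financial and health outcomes, where chance differences could be declared effects. No planned sensitivity analysis would reveal either problem.

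**Working it through.** **The plan's own figure.** The article gives no standard error, intracluster correlation (ICC) or error rate for the clustering. The nearest figures are the anticipated detectable effects in Sample size: 0.2 SD (survey) and 0.12 SD (administrative), attributed to experience with similar projects. Assuming 5% two-sided alpha and 80% power, MDES = (1.960 + 0.842) × √(1/n1 + 1/n0).

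- Survey: 64% of 635 is about 406. With an assumed 406 comparators, 2.802 × √(2/406) = 0.197 SD.
- Administrative: with 635 recipients and an assumed six English comparators each, 2.802 × √[(1/635)(1 + 1/6)] = 0.120 SD.

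Both match simple two-group arithmetic without clustering, so they do not settle the point.

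**Survey model, if clusters are authority × cohort.** Let p be the treated share in an authority and S the sum of residuals in its treated cell.

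1. Authority fixed effects force the authority's residuals to sum to zero, so the comparator cell sums to −S.
2. After removing authority means, treatment equals (1−p) for treated people and −p for comparators. The cell scores are (1−p)S and pS.
3. As one cluster the authority contributes S². As two clusters it contributes [(1−p)² + p²]S².
4. SE ratio = √[p² + (1−p)²], and false-positive rate = 2[1 − Φ(1.96 × ratio)].

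| p | SE ratio | False positives |
|---|---|---|
| 0.50 | 0.707 | 16.6% |
| 0.60 | 0.721 | 15.8% |
| 0.75 | 0.791 | 12.1% |

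No ICC is needed. The result is exact without other covariates. Simulation with the baseline outcome included (1,500 datasets per setting, 22 authorities, 406 v 406) gave a ratio of the two standard errors of 0.707–0.708. False positives were 16–18% with the usual small-sample correction. At 406 v 150 they were 12–14%. Clustering by authority with t on 21 df gave 4–6%.

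**Survey model, if time period is the endline wave.** Every row shares one period, so the clusters are the 22 authorities and false positives are the same 4–6%.

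**Administrative model, two periods.** For an authority's before and after means, the variance of the change is V1 + V0 − 2C. Authority × period clusters estimate V1 + V0 only. With equal variances and correlation r between the two means, SE ratio = 1/√(1−r). For example, with no authority effect and within-person correlation 0.6, 1/√0.4 = 1.58.

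Simulation used 21 Welsh and 41 English authorities (the first matching option, taking its 41 matches as 41 English authorities), an assumed 30 people each and 500 datasets per setting. The ICC and within-person correlation are assumed. Authority characteristics explain half the authority variance unless stated.

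| ICC | Within-person correlation | Estimated/true SE, authority × period | False positives |
|---|---|---|---|
| 0 | 0 | 0.97 | 7.2% |
| 0 | 0.6 | 1.61 | 0.0% |
| 0.01 | 0 | 1.06 | 3.2% |
| 0.05 | 0 | 1.27 | 1.4% |
| 0.05, characteristics explain 90% | 0 | 1.13 | 3.2% |
| 0.05 | 0.3 | 1.54 | 0.2% |
| 0.10 | 0.6 | 2.46 | 0.0% |

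Where authority-period shocks dominated, the ratio was 1.00. With several years and autocorrelated authority shocks it was 0.89–1.12. Clustering by authority gave ratios of 0.94–1.06 and false positives of about 4–8%, judged against 1.96 without a t correction. Simulation error on a 5% rate is about √(0.05 × 0.95/500) = 1 percentage point.

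**Power.** An effect with 80% true power keeps Φ(2.802 − 1.96 × 1.27) = 62% at a ratio of 1.27, and Φ(2.802 − 1.96 × 1.54) = 41% at 1.54.

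**The case against.** A reader might infer that both models give wrong standard errors outright, with 17% false positives for the surveys and far too wide, low-powered results for the administrative data. The documents do not support that.

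**Survey.** The article defines the survey periods as baseline and endline for both groups. Cohort is carried by the treatment indicator and is never called a time period. On that definition the written rule already is clustering by authority. The rationale about where treatment varies stands only in the administrative model. The comparator survey size is not given, so even on the cohort reading 17% is not fixed. All of this stands.

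Against it, the qualifier would then do nothing in the survey model. The cohorts also reach age 20 in different calendar years (July 2024–June 2025 and July 2025–June 2026), so anyone coding period as calendar year would reproduce the cohort split. The text is ambiguous rather than wrong.

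**Administrative.** No ICC, within-person correlation or serial correlation is stated. Personal and authority covariates will absorb some persistence. The period indicator only marks when the intervention is active, so the data need not be limited to two periods. This defeats any claim about size, and with several years it defeats a firm claim about direction. It does not rescue the clustering unit, which ignores covariance that the design creates.

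**Conclusion.** The concern holds in a limited form.

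- **Administrative model:** the stated unit is wrong. With two periods the standard errors are generally too wide. The excess is about 0% with no persistence or dominant authority-period shocks, 27% at ICC 0.05, and about 150% at ICC 0.10 with within-person correlation 0.6. All of these inputs are assumed. With several autocorrelated years the errors can be slightly too small. That most power is lost is one possible outcome, not a finding.
- **Survey model:** the wording is unsafe. The standard error is about 29% too small, with about 17% false positives, only if clusters are authority × cohort and cohorts are equal in size; at 75/25 the false-positive rate is about 12%. On the baseline/endline reading there is no error.

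A primary specification whose false-positive rate is about 5% or about 17% according to how one phrase is coded should be settled before analysis.

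**What to change.** In both primary models, delete the time-period qualifier and state that errors are clustered by local authority, with all cohorts and periods of an authority in one cluster. Remove the parenthetical rationale from the administrative model. With about 22 Welsh clusters, use a small-sample method: t on G−1 degrees of freedom (G = number of clusters) with a CR2 variance, or a wild cluster bootstrap. Make the same change in the analysis plan.

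The cost is one line of text and code, with no new data. Survey intervals become up to about 1.4 times wider (1/0.707) than under authority × cohort clustering, and do not change if the endline reading was intended. Authority clustering does not capture shocks common to a whole cohort or to Wales. That is a separate limitation to state alongside the results.
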